## Abstract

**Background:**

Atrial fibrillation (AF) is an arrhythmia that is prevalent globally, and its incidence grows exponentially with aging. Non-vitamin K antagonist oral anticoagulants (NOACs) have been developed in recent years, and it challenges the supremacy of warfarin for thromboembolism prophylaxis in AF. Nevertheless, there are limited data specifically evaluating the real-life use of NOACs in elderly patients with AF in China.

**Methods:**

This is a national, multicenter, non-interventional, cross-sectional study that enrolls patients with AF aged 75 years and above from 31 institutions across China. Data were collected using the Hospital Information System. The primary outcomes include (1) profiles of NOAC use in the elderly; (2) frequency of inappropriate NOAC use based on guidelines and approved labeling recommendations; (3) exploring potential risk factors related to NOACs inappropriate use; and (4) creating a prediction tool for inappropriate NOACs use.

**Conclusion:**

The results of this study reveal the prevalence, risk factors, and corresponding prediction tool of inappropriate NOACs use in older patients with AF in China, as well as provide valuable insights into the clinical application of NOACs in high-risk populations in the real-world setting.

**Clinical trial registration:**

www.ClinicalTrials.gov, identifier: NCT 05361889.

## Introduction

Atrial fibrillation (AF) is an arrhythmia that is prevalent globally, and its incidence grows exponentially with aging (1). AF increases the risk of stroke and its sequelae. It also leads to severe complications, such as impaired quality of life, heart failure, dementia, disability, and even death. More frequent hospitalization and treatment of these complications substantially increase the economic burden of the disease (2–5).

Oral anticoagulants (OACs) are the cornerstone of stroke and/or systemic embolism (SE) prevention for patients with non-valvular atrial fibrillation (NVAF) (6, 7). Although dose-adjusted warfarin has been the primary treatment for oral anticoagulation for decades, non-vitamin K antagonist oral anticoagulants (NOACs) have been developed more recently and have challenged the supremacy of warfarin for thromboembolism prophylaxis in NVAF (8–11). NOACs comprise dabigatran (factor IIa inhibitor), rivaroxaban, apixaban, and edoxaban (factor Xa inhibitors), and each of these agents has been proven to be equivalent to or even better than warfarin in terms of effectiveness and safety for stroke prevention in NVAF (12). Current guidelines recommend NOACs as the first-line OAC agents, including for the older adult population (6, 7, 12, 13).

Although advanced chronological age by itself is not a contraindication for anticoagulation in AF, in the real clinical context, the appropriate use of NOAC prescriptions is still challenging for several reasons. First, on the subjective side, many clinicians are hesitant to comply with approved NOAC dosing recommendations for older adults due to concerns posed by frailty, liver or kidney function impairment, polypharmacy, complex comorbidities, prior falls, contraindications, and history of bleeding or potential bleeding risk (14). Second, dosages may be varied to account for ethnic factors. For instance, Asian patients with AF tend to be leaner and shorter and have a greater bleeding risk. This population often receives off-label dose-reduced NOAC more frequently than in Western countries (15). Third, approval was granted by the NOACs' National Medical Products Administration (NMPA) at specific doses as adjusted for age, renal function, body weight, or concomitant administration of other drugs. Therefore, the optimal use of NOACs depends on a thorough understanding of drug labels and the knowledge of definitive guidelines and consensus opinions (16). Finally, some hospitals do not have reliable access to important NOAC formulations (17), precluding their rational use. In previous studies, such inappropriate use of NOACs was problematic because it is associated with adverse events and harmful clinical outcomes, including an increased risk of stroke, thromboembolism, cardiovascular hospitalizations, bleeding, and even all-cause mortality (18, 19).

Since most available data on NOAC practices have been established within the framework of a cardiology setting and in the general population, data on Chinese-specific real-life NOACs use, such as in older adults, are underrepresented. Of note, older Chinese individuals with AF account for a high percentage of the total number of patients with AF. This population is considered to be more susceptible to bleeding. The net clinical benefit of vitamin K antagonist (VKA) use in older adults with AF is barely satisfactory (20). Therefore, collecting data on case mix, clinical characteristics, and treatment for older adults with AF is valuable for improving the management of OAC use in real-world practice. In addition, some studies explored risk factors that influence the appropriateness of NOACs. However, they did not establish the related prediction model (21, 22). Therefore, we will conduct a study to (a) investigate profiles of NOAC use in older individuals, (b) determine the rate of inappropriate NOAC use, (c) explore potential risk factors related to inappropriate NOAC use, and (d) conduct a model for inappropriate use of NOACs.

## Materials and methods

### Data sources

This study is proposed as a national, multicenter, non-interventional, cross-sectional study. Individual patient data will be obtained from the ReAl-life multIceNter outcomes registry for Better antithrOmbotic strategies in patients With AF (RAINBOW-AF), an ongoing national AF registration conducted at 31 secondary- or tertiary-care hospitals in China. The purpose of the RAINBOW-AF registry is to collect medical records data of contemporary patients with AF and to determine the relationship between comprehensive assessment and better anticoagulation outcomes in patients with AF. In this study, we will include older adults (aged ≥75 years) who will be receiving a NOAC for NVAF. Considering that this population is regarded as high-risk in the stroke risk-stratification tool (CHA_2_DS_2_-VASc score of at least 2) for NVAF, all selected patients will have strong indications for anticoagulation. The study initiative will be performed based on the Hospital Information System (HIS) (Figure 1). As part of the assessment, this study will be applied for the expansion and spread of a quality promotion initiative for a better NOAC strategy.

**Figure 1 F1:**
[figure not shown]
Design schematic of this registry. NOAC, non-vitamin K antagonist oral anticoagulant. a: Including the following details: basic information, disease information, history, latest laboratory data, co-administrations with NOACs, risk factors for thromboembolism (CHA_2_DS_2_-VASc score), and risk factors for bleeding (HAS-BLED score).

### Site selection

The study will be carried out using data given by inpatients from 12 provinces, two municipalities, and one autonomous region across mainland China, with a focus on regions and medical staff features. Suitable site enrollment will be adopted to guarantee geographic heterogeneity and diversity across practice categories (e.g., secondary graded and tertiary hospitals; teaching and general hospitals) and prescriber type (e.g., general practitioner, neurologist, cardiologist, electrophysiologist, and other specialists). In this way, we expect to register a representative sample of patients with NVAF in mainland China; this will limit any bias introduced by the selection of patient criteria, physician specialty, or extent of experience. Around 31 recruitment sites will be activated to select participants for the study.

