### Patient recruitment criteria

Eligibility criteria include the following: inpatients with complete data sets; age ≥75 years; diagnosis of AF confirmed by electrocardiogram; use of Holter monitor, pacemaker, implantable device or clinic note, or hospital record of such intervention; or documentation of NOAC therapy for AF regardless of prescriber within the past 3 months. For multiple related admissions, each admission data will be recorded to avoid an omission. To minimize the deviation in the selection of the population and to obtain more sufficient information, the outpatient follow-up data after discharge will also be documented using HIS (Table 1).

**Table 1 T1:** Inclusion and exclusion criteria.

**Inclusion criteria**	**Exclusion criteria**
• Inpatients with complete data sets. To minimize the deviation in the selection of the population and obtain more sufficient information, the outpatient follow-up data after discharge will also be documented *via* Hospital Information System	• AF resulting from reversible causative factors (e.g., thyroid disease, postoperative AF, pulmonary embolism)
• Aged ≥ 75 years	• Have additional indication for anticoagulation treatment apart from AF (e.g., venous thromboembolism, hip/knee replacement surgery, left atrial/ventricular thrombus)
• Diagnosed with AF (e.g., by electrocardiogram, Holter monitor, pacemaker, implantable device, or a history of these interventions in any clinic note or hospital record)	• Bleeding history in critical organs (e.g., intracranial, intraocular, or gastrointestinal bleeding)
• To accept a prescription of NOAC therapy for AF whoever the prescriber within the past 3 months (with the rationale that such patients may have exceptional circumstances preventing long-term anticoagulation or lack of an appropriate indication for long-term anticoagulation)	• Current participation in an ongoing clinical trial of NOAC anticoagulation for AF
• For multiple related admissions, each admission data will be recorded to avoid an omission. For example, patients with variable bleeding factors that could be a relative contraindication or an absolute contraindication that could still be inappropriately used	• Illogical data, missing or insufficient data

*AF, atrial fibrillation; NOAC, non-vitamin K antagonist oral anticoagulant*.

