### Data collection

Data will be entered into a web-based case report form, enabled with dynamic data reviews for patient features, expected data ranges, and mandatory fields. It will be derived primarily from three different sources: patients' electronic medical records (including demographics, clinical characteristics, medical management, laboratory measurements, imaging parameters, and drug information), the grade level of treating physicians, referring to the clinical expertise or academic background of clinicians, and the availability of NOACs at each hospital. The specific details include participants' sex, age, body weight, lifestyle, comorbidities (such as diabetes, coronary heart disease, and heart failure), history, latest laboratory data, and risk factors for thromboembolism and bleeding. In addition, co-administration of drugs (such as antiplatelet agents and antiarrhythmic therapy), appearances after NOAC treatment (incidence of inappropriate use), the expertise of physicians, and NOAC availability from that institution will also be documented (Table 2).

**Table 2 T2:** Details of data collection.

**Data collection**	**Interpretation**
• Basic information	Participants' sex, age, body weight, marital status, lifestyle (current smoking and drinking status), educational status, place of residence (rural or urban)
• Disease Information	Type of AF, comorbidities (correlate with stroke and bleeding risk, e.g., anemia, MI, PAD), procedures or surgical history (PCI, CABG, or RFCA)
• History	History of thromboembolism and related hemorrhagic events (major bleeding is defined based upon ISTH criteria and incidences apart from major bleeding are considered as non-major bleeding), fall history
• Latest laboratory data	Serum creatinine levels, hemoglobin, bilirubin, liver function (Child-Pugh score), and renal function (CrCl, calculated using Cockroft-Gault formula)
• Co-administration with NOACs	NOAC medication type, antiplatelet agent, interacting combination medications with NOACs, such as antiarrhythmic therapy, itraconazole, ketoconazole, ritonavir, etc.
• Risk factors for thromboembolism (CHA_2_DS_2_-VASc score)	CHA_2_DS_2_-VASc score is a rating of risk for stroke in patients with AF, items of 1 point each for congestive heart failure, hypertension, diabetes mellitus, vascular disease, Age 65–74 years, sex category [female], and 2 points each for a history of a stroke, TIA, or age ≥ 75 years)

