High-quality anticoagulant treatment is crucial in guaranteeing the effectiveness and safety of OAC administration in AF patients. The benefits of OACs in NVAF may be impossible to achieve if anticoagulant regimens are prescribed inappropriately (27). As NOAC use has become more pervasive, off-label prescribing has become a global issue. Several studies have outlined the adverse clinical consequences of off-label prescribing. The ENGAGE AF-TIMI 48 trial illustrated the outcome of under-dosing of edoxaban (11). The edoxaban 30/15 mg group posed a significantly higher ischemic stroke risk when compared to the well-controlled vitamin K antagonist group; this resulted in the disapproval of this dosing regimen for clinical application (11). In the ORBIT-AF II registry, off-label doses of NOACs presented an increased risk for adverse events than the recommended NOAC dosage protocols (27). In particular, NOAC over-dosing was associated with increased all-cause mortality, while NOAC under-dosing was associated with higher rates of hospitalization for cardiovascular conditions (27). Another study demonstrated that inappropriate NOAC prescriptions were more likely to occur in the older adult population (28). This is the most worrisome finding because the risk of stroke increases significantly with age. Inappropriate dosage exposes high-risk patients to potential hazards of disabling or even fatal strokes.

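### Hospitalised NOAC users aged 75 or over cannot represent NVAF patients in mainland China; for NOACs started before admission, selection on admission and undated predictors may bias the rate and the risk factors

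*Protocol article*

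**What the plan says.** **Claimed population.** Site selection states "we expect to register a representative sample of patients with NVAF in mainland China" and argues that the mix of sites and prescribers will limit selection bias. The Discussion repeats the idea, describing patients as well represented at all levels of care.

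**Sampled population.** The same Site selection section opens with "The study will be carried out using data given by inpatients from 12 provinces". Patient recruitment criteria require "inpatients with complete data sets", age 75 or over, and, in Table 1, "To accept a prescription of NOAC therapy for AF whoever the prescriber within the past 3 months". Critical-organ bleeders and records with illogical, missing or insufficient data are excluded. The stated remedy for selection is that "the outpatient follow-up data after discharge will also be documented using HIS".

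**Link from outcome to admission.** The Introduction says of inappropriate NOAC use that "it is associated with adverse events and harmful clinical outcomes, including an increased risk of stroke, thromboembolism, cardiovascular hospitalizations, bleeding". The Discussion adds that "NOAC under-dosing was associated with higher rates of hospitalization for cardiovascular conditions".

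**Predictors.** Table 2 collects "History of thromboembolism and related hemorrhagic events", the latest laboratory data (including haemoglobin and creatinine), CHA2DS2-VASc and HAS-BLED. HAS-BLED itself scores stroke and bleeding history. Predictors and outcomes names both scores as sources of candidate variables. No item is dated relative to the prescription being judged.

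**Which prescription is judged.** This is not fixed. Table 1 admits prescriptions from the previous 3 months. Data sources speaks of patients who will be receiving a NOAC. Sample size calculation places outcome evaluation during the hospital stay, and Quality control ties outcomes to the first discharge.

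**The concern.** Three problems follow, and they differ in strength.

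1. The claimed population and the sampled population differ. A NOAC user who was never admitted cannot enter at any site, and follow-up after discharge covers only people who were admitted first.
2. If the NOAC was started before admission, being in the sample may depend on whether it was used appropriately, because the protocol associates inappropriate use with the events that lead to admission. The rate of inappropriate use, which is primary outcome (b), could then differ from the rate among older NOAC users generally.
3. In those same patients, a stroke, a non-critical bleed or a fall in haemoglobin that followed the prescription can be recorded as history or as a latest value, and then tested as a risk factor for that prescription. Such information does not exist when the drug is prescribed. That weakens a tool which the Discussion intends for routine practice to flag patients at risk.

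**Working it through.** **The plan's own precision figure.** For one proportion, n = 1.96² × p(1 − p) / d², with d = 0.02 from the 2% error range in Sample size calculation.

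- p = 0.20 gives 1,537 and p = 0.194 gives 1,502.
- p = 0.25 gives 1,801 and p = 0.40 gives 2,305.

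The stated 1,500 is therefore reproduced only near p = 0.20. No expected rate of inappropriate use is given. What matters here is the 2-point margin, used below as the yardstick for bias.

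**Inputs for the selection check.** True rates of 25% and 40% are illustrations from two cohorts cited in the Discussion (nearly a quarter inappropriate; about 60% label adherence). They are not design inputs. R is the ratio of the probability of entering the sample, inappropriate versus appropriate users. The documents give no value, so a range is assumed.

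**Formula.** Observed rate = pR / (pR + 1 − p), for patients whose NOAC preceded admission.

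| R (assumed) | True 25% | True 40% |
|---|---|---|
| 0.8 | 21.1% | 34.8% |
| 0.9 | 23.1% | 37.5% |
| 1.1 | 26.8% | 42.3% |
| 1.25 | 29.4% | 45.5% |
| 1.5 | 33.3% | 50.0% |
| 2.0 | 40.0% | 57.1% |

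**R needed for a 2-point shift.** R = q(1 − p) / [p(1 − q)], where q is the shifted rate.

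- p = 0.25, up: 0.27 × 0.75 / (0.25 × 0.73) = 1.11. Down: 0.23 × 0.75 / (0.25 × 0.77) = 0.90.
- p = 0.40, up: 0.42 × 0.60 / (0.40 × 0.58) = 1.09. Down: 0.38 × 0.60 / (0.40 × 0.62) = 0.92.

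In the whole sample the shift is diluted according to the share of NOACs started in hospital, which the protocol does not state.

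**Direction.** Let exclusions and the complete-data rule retain different shares of the two groups, so that R becomes R × (retained, inappropriate) / (retained, appropriate). With a true rate of 25% and R = 1.25:

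- equal retention gives 29.4%;
- 80% versus 95% gives R = 1.25 × 0.80 / 0.95 = 1.05 and an observed rate of 26.0%;
- 70% versus 95% gives R = 0.92 and 23.5%.

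The retention figures are assumed. They show that an upward shift can be cancelled or reversed.

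**Undated predictors.** Suppose earlier history is unrelated to appropriateness (true odds ratio 1), with prevalence h in both groups, and events after the prescription occur with probability e. The recorded flag then has prevalence h + (1 − h)e. Take h = 10% and e = 5% in appropriate users:

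- appropriate users: 0.10 + 0.90 × 0.05 = 14.5%;
- event risk ratio 1.5 in inappropriate users: 0.10 + 0.90 × 0.075 = 16.75%, apparent odds ratio 1.19;
- risk ratios of 1.25 and 2.0 give 1.09 and 1.38.

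Across h of 10–20%, e of 2–10% and risk ratios of 1.25–2.0, the apparent odds ratio runs from 1.02 to 1.66. All inputs are assumed.

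**The case against.** The strongest reply concerns time order. If the regimen judged is the one given in hospital or at discharge, as Sample size calculation and Quality control suggest, admission precedes the outcome. A stroke that caused the admission is then genuine prior history and is known at prescribing. This stands for NOACs started in hospital, and the point does not extend to them. It does not clear the rest, because prescriptions from the previous 3 months also qualify and the protocol neither separates the groups nor says which prescription is judged.

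A reader might infer that the rate is inflated. The documents do not support that. They give no admission ratio, they exclude intracranial, intraocular and gastrointestinal bleeders, and the Introduction also links inappropriate use with death, which removes patients before sampling. The cited links are themselves associations. Nor can it be said that under-dosing will be over-represented.

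A reader might also infer that the protocol reads effects as causes. Primary outcomes and Statistical analyses speak of correlation and risk factors. Only the Discussion's reference to influencing factors is looser.

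Finally, history ordinarily means prior history, and item dating may sit in a data form that is not shown. That is fair and reduces the weight of the timing point. It does not cover laboratory values described as latest, or scores computed at an unstated time. Nothing says that follow-up data will be used as predictors, but nothing keeps them out.

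On representativeness, the entry criteria are stated openly and Strengths and limitations asks for validation in outpatients. That caveat concerns the prediction model, not the rate.

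**Conclusion.** The concern holds in limited form. The representativeness claim contradicts the entry criteria, and this needs no assumption. Bias in the rate from selection on admission is possible for NOACs started before admission. Its direction is unknown, though upward is plausible. Its size cannot be derived from the documents, but under the assumed model an entry ratio of about 1.1 upward, or 0.9 downward, in those patients matches the planned 2-point error range. For the same patients, information arising after the prescription can enter the risk-factor and prediction models. The apparent odds ratios of 1.02 to 1.66 and the shifted rates in the table are illustrations, not estimates. The point should be settled before analysis; it does not invalidate a study of hospitalised NOAC users.

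**What to change.** 1. In Site selection, and in the matching Discussion text, restrict the stated inference to hospitalised NOAC-treated NVAF patients aged 75 or over at the participating hospitals.
2. State which prescription is judged. Report the rate separately for NOACs started before and during admission, and for admissions due to stroke, bleeding or cardiovascular causes versus other admissions.
3. Use as predictors only events, score items and laboratory values dated before the judged prescription. Record later events and outpatient follow-up separately, and keep them out of the risk-factor and prediction models.

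The cost is a few form fields and table rows. Table 2 lists neither admission reason nor event dates, so their availability in the hospital system needs confirming. The subgroups will be smaller and their intervals wider, apparent model performance may fall, and the claim will be narrower. No new sites or patients are needed.

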### Patient recruitment criteria

Eligibility criteria include the following: inpatients with complete data sets; age ≥75 years; diagnosis of AF confirmed by electrocardiogram; use of Holter monitor, pacemaker, implantable device or clinic note, or hospital record of such intervention; or documentation of NOAC therapy for AF regardless of prescriber within the past 3 months. For multiple related admissions, each admission data will be recorded to avoid an omission. To minimize the deviation in the selection of the population and to obtain more sufficient information, the outpatient follow-up data after discharge will also be documented using HIS (Table 1).

**Table 1 T1:** Inclusion and exclusion criteria.

**Inclusion criteria**	**Exclusion criteria**
• Inpatients with complete data sets. To minimize the deviation in the selection of the population and obtain more sufficient information, the outpatient follow-up data after discharge will also be documented *via* Hospital Information System	• AF resulting from reversible causative factors (e.g., thyroid disease, postoperative AF, pulmonary embolism)
• Aged ≥ 75 years	• Have additional indication for anticoagulation treatment apart from AF (e.g., venous thromboembolism, hip/knee replacement surgery, left atrial/ventricular thrombus)
• Diagnosed with AF (e.g., by electrocardiogram, Holter monitor, pacemaker, implantable device, or a history of these interventions in any clinic note or hospital record)	• Bleeding history in critical organs (e.g., intracranial, intraocular, or gastrointestinal bleeding)
• To accept a prescription of NOAC therapy for AF whoever the prescriber within the past 3 months (with the rationale that such patients may have exceptional circumstances preventing long-term anticoagulation or lack of an appropriate indication for long-term anticoagulation)	• Current participation in an ongoing clinical trial of NOAC anticoagulation for AF
• For multiple related admissions, each admission data will be recorded to avoid an omission. For example, patients with variable bleeding factors that could be a relative contraindication or an absolute contraindication that could still be inappropriately used	• Illogical data, missing or insufficient data

*AF, atrial fibrillation; NOAC, non-vitamin K antagonist oral anticoagulant*.

Exclusion criteria include NVAF due to reversible causes (e.g., thyroid disease, postoperative AF, and pulmonary embolism), having an additional indication for anticoagulation treatment apart from AF (e.g., venous thromboembolism and hip/knee replacement surgery), bleeding history in critical organs, current participation in an ongoing clinical trial of NOAC anticoagulation for AF, and incomplete information (illogical data and missing or insufficient data); any patients with such history will also be excluded.

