### Evaluation of the appropriate NOACs use

Different nations do not always adopt the standard indications for NOAC prescription. Local policies, such as formulary committees, regulatory approval, and cost-effectiveness, all influence NOAC labeling recommendations (23). In this study, we will adopt an adaptive design to account for a summary of product characteristics, and analyze prevalent NOAC strategies based on indications, NOAC selection, or dosages (Figure 2). We use the recommendations given by NMPA for each agent and the 2021 European Heart Rhythm Association (EHRA) practical guide on the use of NOACs for patients with AF (24). Patients for whom the selected NOAC was contraindicated can be categorized as inappropriate use. If there exist no absolute contraindications, the protocol can evaluate appropriateness according to patient-specific features, like age, weight, renal function, Child-Pugh classification, specific drug–drug interactions, hemoglobin level, and bleeding risk. In cases of discrepancy between the EHRA recommendations and the NMPA recommendations, we adopt the NMPA-approved label recommendations as the standard for determining the appropriateness (Table 3). Patients will be classified as either (a) NOAC-appropriate (rational use of NOAC according to the standardized criteria) or (b) NOAC-inappropriate (irrational use of NOAC according to the standardized criteria).

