Since apixaban has not been fully studied in Chinese populations, the NMPA did not approve the NVAF indication for apixaban; thereby, we have excluded it from this study. Rivaroxaban, given 15 mg daily (or 10 mg, based on creatinine clearance rate [CrCl]), in combination with clopidogrel, was also used in patients with AF and recent percutaneous coronary intervention (PCI) or acute coronary syndromes (ACS) in the PIONEER AF-PCI trial. Therefore, we considered that both doses are appropriate for such patients in our study. The NMPA recommends a daily dose of 220 mg for dabigatran, which can be given to patients with CrCl 30–50 ml/min, aged ≥75 years, or with increased bleeding risk. The NOAC prescription was deemed reasonable for patients aged ≥75 years.

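### The rate of inappropriate NOAC use is estimated after removing apixaban users and patients with critical-organ bleeding history, two groups defined by features that the study's own standard judges

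*Protocol article*

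**What the plan says.** All places are in the Protocol article.

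- **Outcome standard** (Evaluation of the appropriate NOACs use). Use is judged on indication, choice of agent and dose. "Patients for whom the selected NOAC was contraindicated can be categorized as inappropriate use". Where there is no absolute contraindication, patient features are weighed, among them "specific drug–drug interactions, hemoglobin level, and bleeding risk". Where the European guide and the Chinese label differ, "we adopt the NMPA-approved label recommendations as the standard for determining the appropriateness".
- **Apixaban** (same section, after Table 3). "the NMPA did not approve the NVAF indication for apixaban; thereby, we have excluded it from this study".
- **Bleeding exclusion** (Patient recruitment criteria, Table 1). "Bleeding history in critical organs (e.g., intracranial, intraocular, or gastrointestinal bleeding"). The text below the table repeats it: "bleeding history in critical organs, current participation in an ongoing clinical trial of NOAC anticoagulation for AF".
- **Inclusion column of Table 1.** Each related admission is recorded so that nothing is omitted. The example given is "patients with variable bleeding factors that could be a relative contraindication or an absolute contraindication that could still be inappropriately used".
- **Predictors** (Data collection, Table 2; Predictors and outcomes). The data include "History of thromboembolism and related hemorrhagic events (major bleeding is defined based upon ISTH criteria", with all other bleeds classed as non-major. HAS-BLED, which has a bleeding-history item, is a candidate predictor.
- **Claims.** The Abstract's conclusion speaks of prevalence in older Chinese patients with AF. Site selection expects a representative sample. Strengths and limitations mentions neither exclusion.

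**The concern.** A prevalence estimate is open to bias when eligibility depends on the features that decide whether a patient is a case. Both exclusions do this to some degree.

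For apixaban the overlap is complete. The reason given for dropping the drug, no approved NVAF indication, is the reason that the label-first standard would score its use for NVAF as inappropriate. Such patients leave both numerator and denominator.

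For critical-organ bleeding the overlap is partial. Bleeding risk is one of the features on which appropriateness is judged, and the exclusion removes the severe end of it.

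At stake are the meaning of the primary rate, which is described as applying to older Chinese AF patients on NOACs generally, and the range over which bleeding history and HAS-BLED can be examined as predictors.

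**Working it through.** **1. What the standard implies for each group**

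| Group removed | Would the standard score it inappropriate? | Basis |
|---|---|---|
| Apixaban for NVAF | Yes, by indication | The label prevails; Table 3 lists apixaban as not approved |
| Critical-organ bleeding history | Some patients; share unknown | Bleeding risk is a criterion; nothing says such history is itself a contraindication |

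**2. Formula.** Let p0 be the inappropriate-use rate in the retained cohort, f the share of otherwise eligible NOAC users removed, and q the rate among those removed.

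Inclusive rate = (1 − f) × p0 + f × q, so inclusive rate − reported rate = f × (q − p0).

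Counting each removed patient once, the shift splits into f_apix × (1 − p0) + f_bleed × (q_bleed − p0). The first term is never negative and is zero only if no apixaban is used for NVAF. The second takes the sign of q_bleed − p0.

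**3. Inputs.** The documents give neither f nor q, and Sample size calculation states no expected rate. All values here are therefore assumptions. For p0 I take 25% and 40%, from two studies cited in the Discussion: nearly a quarter of an older-adult cohort on a potentially inappropriate dose, and about 60% label adherence in a Korean study (1 − 0.60 = 0.40). I let f run from 1% to 10%, and take q as 60%, 100% or equal to p0.

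**4. Shift in percentage points**

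| p0 | q | f = 1% | 2% | 3% | 5% | 10% |
|---|---|---|---|---|---|---|
| 25% | 100% | 0.75 | 1.50 | 2.25 | 3.75 | 7.50 |
| 25% | 60% | 0.35 | 0.70 | 1.05 | 1.75 | 3.50 |
| 40% | 100% | 0.60 | 1.20 | 1.80 | 3.00 | 6.00 |
| 40% | 60% | 0.20 | 0.40 | 0.60 | 1.00 | 2.00 |
| either | = p0 | 0 | 0 | 0 | 0 | 0 |

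For example, with p0 = 25%, q = 100% and f = 5%: 0.05 × (1.00 − 0.25) = 0.0375, so a reported 25% corresponds to an inclusive 28.75%. If q were below p0, which is possible for the bleeding group, the sign would reverse.

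**5. Against the plan's precision.** The plan wants a 2-point margin at 95% confidence. With q = 100%, the shift reaches 2 points at f = 0.02 / 0.75 = 2.7% (p0 = 25%) or 0.02 / 0.60 = 3.3% (p0 = 40%). With q = 60%, it takes f = 0.02 / 0.35 = 5.7% or 0.02 / 0.20 = 10%. A larger sample does not reduce this shift.

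**6. Predictors.** Only critical-organ bleeding is removed. Other bleeds remain and are still classed as major or non-major, and the HAS-BLED bleeding item can still be scored. Both variables are therefore range-restricted rather than lost.

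**The case against.** The apixaban exclusion is stated openly with a reason, so it can be read as a limit of scope: the study concerns the three approved agents. No passage shows that apixaban is used for NVAF at these sites, so its effect could be nil. This stands, and it makes the finding conditional. It does not remove the mismatch, because the outcome and the conclusions are worded for NOACs as a class.

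A reader might go further in four ways that the documents do not support:

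- **That critical-organ bleeders are mostly inappropriate, so excluding them must lower the rate.** No passage says such history contraindicates a NOAC. Table 3 gives dosing regimens, and for dabigatran it lists increased bleeding risk among the conditions where either of two daily doses is accepted after individual evaluation. Some excluded patients could be scored appropriate. The Introduction names bleeding history as a reason clinicians depart from approved dosing, and the Discussion cites it as related to under-dosing. That makes understatement plausible, no more.
- **That bleeding history cannot be assessed at all.** Table 2 and HAS-BLED show otherwise.
- **That the two columns of Table 1 flatly contradict each other.** The inclusion example concerns varying factors across repeated admissions and can be read as compatible with excluding a fixed history. The text does not draw that line, so it needs clarifying.
- **That the remaining rate is mainly about dosing errors.** Indication, choice of agent, contraindications and interactions are still judged in everyone retained.

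There is also a fair argument against putting apixaban users into the prediction model. They would be inappropriate by definition, so drug type would predict the outcome deterministically and could flatter discrimination. I accept that.

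**Conclusion.** The point holds in a limited form. The primary rate describes users of the three approved agents without critical-organ bleeding history, while the plan presents it as the rate in older Chinese AF patients on NOACs.

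The all-NOAC rate is understated if any apixaban is used for NVAF at the sites. This rests on applying the plan's label-first rule to an unapproved indication. For the bleeding exclusion, the direction is plausible but not established.

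The size of either effect cannot be derived from the documents. The 0 to 7.5 points in the table reflect assumed inputs and are not an estimate. They show only that a removed share of about 3% could matter against a 2-point margin if nearly all of those patients were inappropriate.

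Critical-organ bleeding history cannot be assessed as a predictor. Bleeding history and HAS-BLED lose their severe end, but other bleeding history can still be assessed.

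**What to change.** 1. From the Hospital Information System, count the otherwise eligible NOAC users removed by each exclusion, score them with the same algorithm, and report the inappropriate-use rate with and without them.
2. Either make the inclusive rate the headline, or keep the exclusions and restrict the name of the primary outcome, the Abstract's conclusion and the representativeness claim in Site selection to users of the three approved agents without critical-organ bleeding history.
3. The prediction model may stay in the restricted cohort, with that restriction stated.
4. Reconcile the Table 1 example on bleeding contraindications with the bleeding exclusion, and the label-first rule with the removal of apixaban. How these are resolved clinically is for the investigators.

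Cost: some further records to extract and score, a slightly more heterogeneous cohort for the rate, and changes of wording.
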